#### Study duration

We expect to enroll the 193 patients within 2 years of study initiation. Patients will be followed by UCLA Nuclear medicine (phone calls/ secure emails) until either one of the following conditions occur:5 years after the date of initiation of randomization.Biochemical progression.Diagnostic of extra-pelvic metastatic disease by any imaging or biopsy.Initiation of any additional salvage therapy.Death.

### Sample size determination

In our a previous study [38], 52/270 patients (19%) had at least one lesion detected by PSMA PET/CT which was not covered by the standard radiation field that covered both the prostate bed and pelvic lymph nodes (RTOG consensus delineations). Standard SRT would not have resulted in durable disease control because gross disease would have been missed. Therefore, we hypothesized that the incorporation of PSMA PET/CT to SRT planning will improve 5-year PFS survival by 20%. Based on available published literature we estimated the 5 y PFS at 60% with standard SRT [5–9, 12]. Therefore, we assume 5-year PFS to be 60% in Arm 1 (standard SRT) and 80% in Arm 2 (PSMA PET/CT based SRT). We also assume that approximately 13% of subjects randomized to Arm 2 will have extra-pelvic metastasis detected by PSMA PET/CT, and therefore are not curable by SRT directed to the pelvis [38]. Based on these estimates, 193 subjects are required to be randomized in a 1:1.13 ratio (90 in control group and 103 in the PSMA group). Randomized, eligible, sample size in each group is therefore *n* = 90. When the randomized, eligible, sample size in each group is 90, with an estimated total number of events required of 46, an exponential maximum likelihood test of equality of survival curves with a 0.050 two-sided significance level will have 80% power to detect the difference between a PSMA group exponential parameter of 0.0446 (assuming a 5 year failure rate of 20%) and a control group exponential parameter of 0.1022 (assuming a 5-year failure rate of 40%), which equals a constant hazard ratio of 0.436; this assumes a maximum follow-up time of 5 years and a common exponential dropout rate of 0.0211 (assuming 10% 5-year drop-out rate in each group). The planned log-rank test should have similar power to the exponential MLE survival test.

### Allocation sequence generation, concealment mechanism and implementation

UCLA Department of Medicine Statistics Core (DOMStat) will build code to randomly assign patients to control/PSMA groups after the patient eligibility form is filled out in Research Electronic Data Capture (REDCap) [51]. DOMStat will develop reproducible code to randomly generate the allocation sequence. To ensure balance between treatment allocation throughout the study, we will use a blocked randomization of size 6. This block size will be unknown to the nuclear medicine research team and the radiation oncologists when enrolling a patient and the control/PSMA allocation will be masked until after the until after screening/baseline data are entered and filled out in REDCap (no anticipation of the group assignment possible). All the data management such as the randomization allocation will be performed by UCLA Nuclear Medicine Research Team in the REDCap online database.

This is an open label study. Trial participants, care providers, outcome assessors, and data analysts will be aware of the assignment after enrollment in REDCap is completed. The randomization number and assignation will be communicated 1 day after the registration by phone or email to the treating physician and the patient.

### Data collection, management and monitoring

Study database will be developed by DOMStat using REDCap [51], which is supported by the UCLA CTSI program and includes high level data security, access logs, data storage and backup. DOMStat has an extensive computational infrastructure with database and statistical software, desktop computers, and a centralized file server for data storage and backup. The REDCap study database will have validated range checks for data entry fields, branching logic, and rigorous pre-testing to make sure the data are appropriately capture. The UCLA Nuclear Medicine research team will enter all data of each patient into the REDCap database. The UCLA Nuclear Medicine research team will have full access to all interim and final results of the study through the REDCap database and is responsible for the final decision to terminate the trial. There is no planned interim analysis. All the data management will be performed by the UCLA Nuclear Medicine Research Team in the REDCap online database. During the clinical investigation, the UCLA Nuclear Medicine research team will evaluate the progress of the trial, including periodic assessments of data quality and timeliness, participant recruitment, accrual and retention, participant risk versus benefit, and other factors that can affect study outcome. All the datasets generated during the current study will be stored and managed on the UCLA REDCap database. All data generated and/or analyzed during this study will be publicly available (own DOI) after completion of the study and the publication of the article of the final analysis of study. The datasets generated and/or analyzed during the trial will not be publicly available before completion of the study but can be available from the corresponding author on reasonable request. Even if the required number of patients to reach statistical power (*n* = 193) is not met, patients already enrolled in the trial will still be followed for 5 years as this data alone would be valuable and unique.

### Statistical methods

We will use a log rank test to compare PFS time between the two randomized treatment arms. We assume that approximately 13% of subjects randomized to Arm 2 will be found to be ineligible for SRT and will not be included for the primary endpoint analysis. Secondary analyses will utilize Cox-proportional hazards regression models. These models will include terms for treatment as well as appropriate clinical/demographic covariates (e.g., ADT, pelvic LN RT, PSA doubling time, Gleason grade, T stage, age, etc.). Residual analyses will be performed to evaluate the proportional hazards assumptions of the Cox model. As a sensitivity analysis, we will also consider survival models that can account for competing risks (ex. death from other causes).

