## Introduction

### Background

Prostate cancer (PCa) is expected to have an incidence of 161,000 and a mortality of 27,000 in the US in 2017 [1]. Curative treatments for localized PCa include radical prostatectomy or radiotherapy [2]. After failure of local therapy, recurrence is detected by rising serum PSA levels. Biochemical recurrence (BCR) occurs in 20 to 80% of patients within 10 years after radical prostatectomy, with the risk of failure dependent on NCCN risk group, pathologic features, and genomic classification [3, 4]. Locally recurrent disease after radical prostatectomy may be cured by salvage radiation therapy (SRT) [5]. Overall, SRT offers long-term biochemical control in about 50–60% of patients [6, 7], depending on pre-SRT prostate-specific antigen (PSA) [5], RT dose [8] and risk group [9]. Results from RTOG 0534 trial [10], which compared three salvage RT regimens: SRT directed to the prostate bed alone, SRT directed to the prostate bed with 4–6 months of concurrent ADT, and SRT directed to the prostate bed and nodes with 4–6 months of concurrent ADT, was recently presented [11]. Five-year biochemical recurrence free survivals were higher than expected in all arms at 71.1, 82.7, and 89.1%, respectively. Pre-SRT PSA levels were < 1.0 ng/mL in 90% of patients and only 17% of patients enrolled had a pathologic Gleason Score of 8 or higher. It is likely that these findings will impact routine practice [11]. For high-risk patients, however, 5-year BCR after SRT reaches 70% [6, 12, 13].

Intuitively, SRT is only curative if recurrent disease is completely encompassed by the irradiated volumes. Therefore, accurate localization of recurrent disease is critical. However, standard-of-care imaging modalities are too insensitive to identify recurrence sites in time to guide salvage treatment [14–16]. In practice, SRT is commonly initiated in patients with serum PSA levels < 1 ng/mL, a threshold at which standard-of-care imaging is insensitive for detecting recurrence [15]. As such, SRT target volumes are usually delineated in the absence of radiographically visible disease (gross disease). Based on an expert consensus panel the RTOG (Radiation Therapy Oncology Group) published contouring guidelines for both prostate bed and pelvic lymph node (LN) Clinical Target Volumes (CTV) as these regions often harbor occult tumors not seen on standard-of-care imaging [17, 18]. These consensus CTV are applied in ongoing trials and guide routine clinical care.

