#### Salvage radiation therapy management

The treating physician will be asked to describe their general treatment plan prior to randomization. The choice of treating the prostate bed alone vs prostate bed and pelvic lymph nodes, with or without ADT, is at the discretion of the treating physician.

Patients randomized to control arm 1 do not undergo PSMA PET/CT: SRT will be performed as routinely planned per discretion of the treating radiation oncologist in accordance with the initial general treatment plan whenever possible. Any other imaging is allowed for SRT planning if done per routine care.

Patients randomized to arm 2 will undergo a PSMA PET/CT scan before SRT planning.If the PSMA PET/CT scan is negative for BCR site identification: SRT will be performed as routinely planned per discretion of the treating radiation oncologist in accordance with the initial general treatment plan whenever possible. The treating physician is encouraged not to de-escalate therapy as a negative PSMA PET/CT does not mean that the patient has no recurrent PCa, rather that it was unable to be detected by the scan (for example, microscopic disease). Thus, if the initial treatment intent was to treat the prostate bed and pelvic nodes, then this should be pursued even in the absence of PSMA-positive nodes.if the PSMA PET/CT scan is positive for pelvic lesions: SRT can be performed with adapted/extended target volumes to include all pelvic PSMA-positive lesions within the radiation fields. SRT may also be performed with focal dose escalation on the PSMA-positive lesions if feasible. SRT can also be performed as routinely planned in accordance with the initial general treatment plan per discretion of the treating radiation oncologist. Furthermore, a PSMA PET/CT scan showing PSMA-positive disease in one or more pelvic nodes does not exclude the possibility of additional disease in the prostate bed, and vice versa.If the PSMA PET/CT scan detects PSMA-positive lesions outside the pelvis: Treatment management will be performed as per discretion of the treating radiation oncologist. We assume that approximately 13% of subjects randomized to Arm 2 will have PSMA-positive distant metastases. These patients will not be included in analysis of the primary endpoint, and their actual treatment plan will be determined by the treating radiation oncologist.

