#### Randomization and intervention

5)Enrolled patients will be randomized to either the control arm (arm 1) or the PSMA SRT arm (arm 2) in a 1:1.13 ratio. The randomization number and assigned arm will be communicated by phone or email to treating physicians and patients 1 day after the enrollment.6)Patients assigned to arm 2 will be scheduled to undergo a PSMA PET/CT scan at UCLA Nuclear Medicine free of charge prior to radiation therapy planning. DICOM images and reports of PSMA PET/CT scans will be delivered to the treating radiation oncologist.7)SRT will be done per routine care at the treating radiation oncologist institution, and typically takes place over about 2 months. The treating radiation oncologist may change the radiation plan depending on the findings of the PSMA PET/CT scan.

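### The secondary Cox models list ADT and pelvic nodal radiotherapy as covariates without limiting them to the plan made before randomisation; as delivered, both can be changed by the PET result

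*Protocol article*

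**What the plan says.** Statistical methods in the protocol article makes the log-rank test the primary comparison and reserves Cox regression for secondary analyses. Those models are to hold a term for treatment and "appropriate clinical/demographic covariates (e.g., ADT, pelvic LN RT, PSA doubling time, Gleason grade, T stage, age, etc". The list does not separate planned from delivered treatment.

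Four other sections bear on what these two covariates are:

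- Salvage radiation therapy management: "The treating physician will be asked to describe their general treatment plan prior to randomization". The same section leaves the field (bed, or bed plus pelvic nodes) and the use of ADT to the treating physician.
- Randomization and intervention: "The treating radiation oncologist may change the radiation plan depending on the findings of the PSMA PET/CT scan".
- Follow-up: staff may contact treating physicians to identify changes from the initial plan. The four categories are bed or bed plus nodes, each with or without ADT.
- Secondary endpoints measures: change in initial treatment intent is one of the secondary endpoints.

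**The concern.** The trial asks whether planning with PSMA PET/CT improves the outcome of SRT. One way in which the scan can act is by changing what is given. If nodal radiotherapy or ADT is added because of a positive scan, that addition is a consequence of randomisation to Arm 2. A Cox model that holds delivered ADT and delivered nodal radiotherapy constant compares the arms as if that consequence had not occurred, so it does not estimate the total effect of PET-based planning.

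There is a second problem. Intensification after a positive scan also marks patients with visible disease. Among patients who received the same treatment, the two arms then differ in underlying disease, and the balance given by randomisation is lost.

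Field and ADT are treatment choices that readers will expect to see accounted for, so the adjusted hazard ratio is likely to draw attention. The study is open label, with data analysts aware of assignment, and the covariate list is open-ended. The definition should therefore be settled in advance.

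**Working it through.** **1. The plan's own figures.** Inputs from Sample size determination: 5-year PFS of 60% and 80%, two-sided alpha 0.05, 80% power, 90 analysed per arm, 46 events, 5 years of follow-up, dropout rate 0.0211.

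- Hazards: −ln(0.60)/5 = 0.1022 and −ln(0.80)/5 = 0.0446.
- Ratio: 0.437 unrounded; 0.0446/0.1022 = 0.436 from the rounded rates, as stated ("which equals a constant hazard ratio of 0.436").
- Schoenfeld events: 4(1.960 + 0.842)²/(ln 0.437)² = 4 × 7.85/0.686 = 45.8, so 46. Power at 46 events is 80.2%.
- Exponential maximum likelihood test with 90 per arm: 79.9% to 80.8%, depending on the form of the variance.

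The plan's figure reproduces. No covariate enters it, so the point below does not touch it.

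**2. When each covariate is fixed.**

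| Covariate | Fixed before randomisation? |
|---|---|
| PSA doubling time, Gleason grade, T stage, age | Yes, if the pre-treatment value is used |
| ADT and nodal RT as planned | Yes; the general plan is requested before randomisation |
| ADT and nodal RT as delivered | No; open to change after the scan in Arm 2 |

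In the control arm, and after a negative scan, treatment is to follow the initial plan whenever possible. Delivered and planned treatment should therefore part mainly among scan-positive patients in Arm 2, where the difference depends on arm.

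**3. Size as a function of the mediated share.** Let f be the share of the log hazard ratio that acts through ADT and nodal RT. The protocol gives no value, so f is an assumption shown over its whole range. If adjustment removes exactly that share, HR(adjusted) = 0.437^(1−f). As a yardstick for the signal left, power at 46 events is Φ(|ln HR|·√46/2 − 1.96). This is not the power of the trial's primary test.

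| f | Adjusted HR | Power at 46 events |
|---|---|---|
| 0 | 0.437 | 80% |
| 0.25 | 0.537 | 56% |
| 0.50 | 0.661 | 29% |
| 0.75 | 0.813 | 10% |
| 1 | 1.000 | 2.5% |

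**4. Direction.** Step 3 leaves out selection, so Cox models were simulated with 300,000 patients per arm, control 5-year PFS set to 60%, 5 years of follow-up and dropout 0.0211. One indicator stands for intensified treatment (ADT or nodal RT). In Arm 2, patients with PET-visible disease may be moved to it. All scenario inputs are assumptions.

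| Scenario | Unadjusted HR | Adjusted for plan | Adjusted for delivered |
|---|---|---|---|
| All benefit through intensification (HR 0.25) | 0.641 | 0.624 | 0.996 |
| Intensification 0.4, other routes 0.6 | 0.449 | 0.441 | 0.602 |
| Same, visible disease prognostic (HR 3) | 0.410 | 0.402 | 0.479 |
| Intensification inert, other routes 0.5, visible disease HR 4 | 0.530 | 0.530 | 0.495 |
| Intensification 0.85, other routes 0.5, visible disease HR 6 | 0.515 | 0.514 | 0.464 |
| Intensification 0.6, other routes 0.5, visible disease HR 6 | 0.442 | 0.440 | 0.426 |

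The first row's 0.996 follows from its assumption of full mediation and is no evidence about this trial. In the last three rows, adjustment charges part of the worse prognosis to the treatment given, and the arm effect moves away from 1. Adjustment for the plan stays within 0.02 of the unadjusted value throughout (largest gap 0.641 − 0.624 = 0.017).

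**The case against.** **The text never says delivered.** The two items stand beside baseline factors, the plan is requested before randomisation, and an analysis plan could settle the definition. It is right that the protocol does not commit to delivered treatment. But this is more than a detail left for later. The article names the covariates, two of them are treatments, and the plain reading of a treatment covariate is treatment given. Either reading needs the same clarification.

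**ADT and nodal RT are not the only routes of benefit.** This stands. Background and Salvage radiation therapy management also name a higher dose to PET-positive disease and extended target volumes. The Rationale argues the 20-point gain from exclusion of patients with M1 disease (13%) and better coverage of out-of-field pelvic lesions (7%), against reference fields that already covered bed and nodes. Simple indicators for ADT and nodal RT would not remove these routes.

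A reader might infer that adjustment erases the effect, pointing to the cited three-arm salvage radiotherapy trial: "Five-year biochemical recurrence free survivals were higher than expected in all arms at 71.1, 82.7, and 89.1%, respectively". The documents do not support that. Those rates come from another trial. A calculation in which outcome depends only on the treatment received returns an adjusted hazard ratio near 1 by construction. Nor does the article say what share of Arm 2 would move to nodes plus ADT; its figure of about half concerns any effect on planning.

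**The direction is not certain.** This also stands, as the last three simulated rows show.

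**Stratifying the primary test.** A reader might go on to ask for a log-rank test stratified by intended plan. The unstratified test is valid after randomisation, about 46 events over four categories could leave sparse strata, and the article describes blocked randomisation with no stratification. That is a preference, not the correction of an error.

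**Conclusion.** The point holds in limited form. The covariate definition is left open to a reading under which the adjusted hazard ratio would not answer the trial's question. Under that reading it could be distorted in either direction, most likely toward 1 if ADT and nodal RT carry part of the benefit and visible disease is not strongly prognostic. The size cannot be fixed from the documents, because it rests on an unknown mediated share and on how strongly scan-prompted intensification marks worse disease. Only the secondary Cox models are affected. The log-rank test, the 46 events and the 193 patients stand as they are.

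**What to change.** In Statistical methods:

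1. Replace the two items by ADT and pelvic nodal radiotherapy as intended in the general treatment plan given before randomisation.
2. State that all Cox covariates are limited to values recorded before randomisation.
3. Report any model with delivered ADT or delivered nodal radiotherapy separately, labelled as a mediation or descriptive analysis and not as an adjusted estimate of the arm effect.

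The cost is wording, since the plan is already requested before randomisation. The one practical check is that the database stores it in a form that can be coded: the article lists the four categories under Follow-up, for tracking changes, and does not say that the initial plan is entered in the same way. Sample size and primary analysis need no change.

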## Discussion

^68^Ga-PSMA-11 PET/CT molecular imaging is highly sensitive to detect and localize PCa BCR. However, it is unclear if incorporation of PSMA PET/CT imaging into the planning of SRT could improve its likelihood of success. No randomized prospective trial has been designed to determine whether PSMA PET/CT can improve 5-year outcomes in patients with early BCR after radical prostatectomy**.** The purpose of this trial is to compare the success rate of SRT in patients with BCR after radical prostatectomy among patients with PSMA PET/CT based SRT planning vs. standard SRT planning.

Potential pitfalls in study design include i) drop-out of patients randomized to the control arm as patients may be able to undergo PSMA PET/CT scans in other institutions; ii) potential FDA approval of PSMA PET imaging probes (Gallium-68-PSMA-11 or Fluor-18-DCFPyL) in the near future which would in essence lead to termination of new enrollment. As PSMA PET/CT imaging may become standard-of-care, randomizing patients to the control arm would no longer be feasible. Therefore, the time period for patient recruitment may be limited (1 to 2 years starting from September 2018). Even if the required number of patients to reach statistical power (*n* = 193) is not met, patients already enrolled in the trial will still be followed for 5 years as this would remain highly valuable and unique data.

Published randomized prospective trials with long-term follow-up demonstrate that the success rate of SRT is enhanced by the addition of concurrent and adjuvant conventional androgen deprivation [6] or first generation antiandrogens [52]. Ongoing trials are now evaluating the role of second-generation systemic therapies that target the Androgen Receptor (NRG GU 006). The magnitude of the impact of adding these systemic therapies to SRT depends on clinicopathologic features including pre-SRT PSA, Gleason Grade, margin status, and genomic classifiers [53]. Moreover, hormonal agents have well known and expected side effects. As such, the expected benefit of adding systemic therapy to SRT may be outweighed by known risks for many patients.

Oligometastatic prostate cancer, variously defined as metastatic disease with between three to five sites of identifiable metastases, is another disease state with rapidly evolving treatment paradigms. STAMPEDE randomized patients with metastatic hormone sensitive prostate cancer to long-term androgen suppression with or without radiotherapy directed to the prostate alone [54]. Pre-planned analyses of patients with limited metastatic disease burden had an improvement in survival [54]. The value of controlling recurrent local disease in patients who have synchronous metastatic prostate cancer is unknown. However, the identification of these patients with modern imaging, such as PSMA PET/CT, will increase. Indeed, we anticipate that 13% of patients randomized to PSMA PET/CT in our trial may fall into this group [38]. The optimal treatment for these patients remains unknown.

This is the first prospective randomized phase 3 trial designed to determine whether a molecular imaging modality, PSMA PET/CT, can improve outcomes after SRT. Like testing the addition of systemic therapies to SRT, testing the addition of PSMA PET/CT to SRT may improve disease control. However, unlike additional systemic therapies, PSMA PET/CT has few if any side effects, minimal risks, and enables better patient selection and disease state identification.

